#### **F. Determination of SVR12 and reinfection by dried blood spot (DBS) specimens**

To determine SVR12, we will compare the sensitivity and specificity of HCV RNA detection by PCR from a venous blood sample collected in standard blood collection tubes with a capillary blood sample collected on DBS. We will use the DBS alone to screen for reinfection two more times, every 12 weeks after SVR12 through the end of the study period.

Twelve weeks after treatment completion, we will collect a venous sample to be processed at the Baystate Laboratory on their routine, clinical platform to detect HCV RNA by PCR. An undetectable RNA at this time point would establish SVR12, also considered cure. A simultaneously collected capillary sample will be processed Molecular Testing Labs (MTL) in Vancouver, WA, according to their validated procedure for DBS processing and detection of HCV RNA by PCR. We will establish sensitivity and specificity of the DBS method, using the detection of HCV RNA by PCR from the venous sample as the gold standard.

After SVR12 has been established, we will collect capillary blood on DBS two more times, every twelve weeks, to be processed by MTL, to screen for reinfection.

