**HCV testing using capillary blood collected on dried blood spot (DBS) cards rather than venous blood can improve the HCV care cascade in rural areas with poor access to phlebotomy.** Screening for HCV antibodies can be easily achieved through point-of-care capillary blood testing. To distinguish active from resolved infection, and hence identify persons in need of treatment, a positive antibody test must be followed up with a molecular test detecting viral RNA. Furthermore, in the future, detection of HCV viremia will be essential for HCV screening, since many of the HCV-infected individuals will have been treated. The need for venipuncture to assess HCV viremia leads to a substantial loss to follow up, even in settings with better access to laboratories and less marginalized populations. Indeed, in our UG3 study 26% of individuals with a positive rapid HCV test did not obtain confirmatory testing, largely because of poor venous access. DBS to detect HCV viremia has been implemented internationally in resource poor settings and in hard-to-reach populations, but has not yet been validated in the U.S. False negatives from capillary blood collected on DBS cards can occur at low titers of HCV viremia, but patients who experience reinfection usually have high HCV viral loads that are detectable, which will be easily detectable in our UH3 study population.

Adoption of DBS in the US has the potential to improve the HCV care cascade, increase treatment and facilitate monitoring for reinfection in at-risk populations in rural and other resource-poor settings. A major barrier to implementation of DBS is limited experience with its use in different settings. The World Health Organization priorities for research include its validation for monitoring treatment response and HCV test of cure (e.g., SVR12), including threshold for detection, diagnostic performance, and impact on linkage to care in different settings, including mobile and outreach-based testing programs.

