### 1. Inclusion Criteria:

- a. Current or past history of drug injection;
- b. Health insurance that will cover HCV medications (study staff will work with those who are eligible but have not signed up for insurance once consented and enrolled in study)
- c. Lives in one of the 10 study counties in NH and VT, and plans to remain in the study region for the next 12 months;
- d. Age 18 years or older;
- e. Speaks English;
- f. Capacity to voluntarily provide informed consent;
- g. Will accept randomized assignment, and participate in follow-up over 12 months;
- h. Will provide releases to access community medical records;
- i. Will provide names and contact information of at least 3 persons for re-contact purposes;
- j. Not previously treated for HCV;
- k. Not pregnant or trying to conceive;
- l. HCV antibody positive on point-of-care rapid test.

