## 4. Study Conditions

**a. Group 1: Enhanced Usual Care (EUC).** At **Visit T1**, eligible participants assigned to EUC will meet the care navigator who will arrange referral for HCV treatment with local or regional clinicians, and receive a copy of their test results and information about the initial dose of vaccine they received to bring to the clinician. The care navigation, vaccination, and provision of test results represent significant enhancements to usual care, and may help reduce the high no-show rate for clinical referrals in this population.

**Care Navigation.** All EUC participants will receive care navigation for HCV treatment. Care navigation will be adapted from existing medical case management services for HIV in consultation with our harm reduction partners. Care navigation will be provided by staff from harm reduction partners and by study staff. Navigation will be tailored to the participant and trauma-informed. The complete manual for HCV care navigation will be

developed in collaboration with harm reduction partners and community stakeholders (including referencing and adapting some of the resources they use for SSP management) in the first quarter of the project.

Care navigation will focus on HCV care coordination and will include maintaining health insurance enrollment, coordination of study visits, provision of harm reduction services, and establishment of a care coordination agreement so the care navigator and study team can communicate with providers and other members of the care team. The Care Navigator will also perform an initial assessment of other needs to address social determinants of health and connect participants to available resources, primarily via referrals to harm reduction partners (e.g. MOUD, primary care, visits to the ED, housing, transportation, employment, etc.). EUC participants will have care navigation services for the duration of HCV treatment or, for those who do not initiate treatment, to a maximum duration of 16 weeks.

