For treatment initiation, we expect 50% or fewer participants in the EUC to initiate treatment, and the MTC intervention to improve initiation to at least 70%. Thus, 220 individuals randomized equally to two groups would provide 86% power to detect a 20% absolute difference between study groups for a test of difference in proportions at  $P < .05$ . This difference is equivalent to an odds ratio of 2.33, or a medium effect size.

For sustained viral response at 12 weeks post-treatment (SVR12), an intent-to-treat approach would include all participants randomized. We expect the success rates to be lower than for the "as-treated" approach, since attrition may occur both at initiation of therapy, as well as completion of therapy. Thus a sample of 110 participants per group would provide about 80% power to detect difference in the proportion of treatment success of 30% in the EUC and 48.5% in the MTC group. This difference is equivalent to an odds ratio of 2.12, which is equivalent to a medium effect size (approximate Cohen's  $d = 0.42$ ). Because the lower treatment initiation rate in the EUC group will favor the MTC group, we also present an as-treated sample size calculation. We expect about 55 patients (i.e., 50% of 110) in the EUC group and at least 77 patients (70% of 110) in the MTC to initiate treatment. Again, we expect the MTC intervention to overcome substantial obstacles to achieving SVR12. As such, a difference in the proportion of participants achieving SVR12 at least as large as 25% is expected. Thus a sample of 132 participants (55 in usual care and 77 in intervention), would provide about 82% power to detect a difference between the MTC intervention and EUC groups of 25% absolute difference (i.e., 65% vs. 40%) for a test of difference in proportions at a critical level of 5%. This difference is equivalent to an odds ratio of 2.79, which is about a medium effect size (equivalent to Cohen's  $d$  of 0.56)

For injection sharing behavior, our UG3 survey found that 77% of HCV-infected PWIDs shared *any* equipment in the 30 days prior, and 66% shared syringes. Using an ITT approach, a sample of 110 participants per group would provide at least 80% power to detect a 19% or greater reduction in sharing behaviors for

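### The protocol names one source for SVR12, a study venous draw, with no fallback to community RNA results; if cured EUC participants miss that visit more often, H2 may be biased toward MTC

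*Protocol*

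**What the plan says.** Protocol section IV.F sets out how SVR12 is determined. Twelve weeks after treatment ends, "we will collect a venous sample to be processed at the Baystate Laboratory on their routine, clinical platform to detect HCV RNA by PCR". It continues: "An undetectable RNA at this time point would establish SVR12, also considered cure". A capillary sample is taken at the same visit, but its stated role is validation of the dried blood spot (DBS) method, "using the detection of HCV RNA by PCR from the venous sample as the gold standard". No other source is named for a missed visit or a failed draw.

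Other parts of the protocol bear on this:

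- Inclusion criterion (h) in section IV.B.1 applies to every participant: "Will provide releases to access community medical records".
- Section IV.B.4 refers EUC participants to local or regional clinicians. Navigation includes "establishment of a care coordination agreement so the care navigator and study team can communicate with providers" and help with coordinating study visits. It is time-limited: "EUC participants will have care navigation services for the duration of HCV treatment", with a cap of 16 weeks for those who never start.
- Section IV.E says that for SVR12 "an intent-to-treat approach would include all participants randomized". Its missing-data paragraph prescribes multiple imputation under MAR, compared with complete-data results. The quality assurance plan in the data and safety monitoring section repeats this.

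**The concern.** The two arms reach the SVR12 visit by different routes. MTC participants have their HCV care, check-ins and follow-up vaccines through the study team and the van. EUC participants are treated elsewhere, and the navigator who coordinates their study visits is no longer provided once treatment ends. The clinician who treated them may test for cure. A participant who already has that result has less reason to travel to the van, in a region where the protocol itself stresses distance and poor transport.

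Such a person is cured, and the evidence sits in a record the study is authorised to read. Under section IV.F as written, though, that person has no observed SVR12. If this happens more often in EUC, H2 partly measures who came back to the van. SVR12 is a primary outcome and the basis of the interim efficacy rule, so its ascertainment should not depend on where treatment was given.

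**Working it through.** **Reproducing the plan's figure.** Inputs from section IV.E: 110 per group, 30% (EUC) against 48.5% (MTC), 5% level, taken as two-sided. The two-proportion normal approximation with pooled variance gives 80.7% power, against the stated figure of about 80%. The planning figure stands and is not in question.

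**Illustration of the ascertainment gap.** The protocol gives no attendance rates, so these inputs are assumptions:

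- True cure is p = 40% in both arms, so there is no real difference.
- A share a of cured participants has a study sample: 80% in EUC and 90% in MTC, or 70% and 90% in a wider case.
- All participants who are not cured have a known outcome.

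*Missing counted as failure* (the protocol does not state this). Observed rate = p × a.

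- EUC 0.40 × 0.80 = 32%; MTC 0.40 × 0.90 = 36%; difference 4 points.
- Wider case: EUC 0.40 × 0.70 = 28%; MTC 36%; difference 8 points.

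*Imputation under MAR using arm only.* In expectation this reproduces the rate among observed participants, p × a / (p × a + 1 − p).

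- EUC 0.32 / (0.32 + 0.60) = 34.8%; MTC 0.36 / (0.36 + 0.60) = 37.5%; difference 2.7 points.
- Wider case: EUC 0.28 / 0.88 = 31.8%; MTC 37.5%; difference 5.7 points.

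Imputation shrinks the spurious difference but keeps its direction, because here missingness depends on the outcome itself.

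**Effect on the test, missing counted as failure** (110 per arm, two-sided 5%). The chance of p < 0.05 with no true difference is 9.6% at 32% against 36%, and 24.5% at 28% against 36%. These are upper illustrations, since the protocol plans imputation.

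**Effect at the interim look.** The efficacy boundary is p ≤ 0.003. With 55 per arm (half of 110) and the same two null scenarios, the chance of crossing is about 0.6% and 1.9%.

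**Equal loss in both arms.** With equal true cure and equal ascertainment, either calculation gives a difference of zero. At the planned 30% against 48.5%, counting missing as failure, power falls from 80.7% to 74% if 10% of cures are missed in each arm, and to 66% if 20% are missed. Equal loss costs power and does not favour MTC.

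**The case against.** The strongest reply is that the text does not produce a bias. Three readings that go further than the documents are tempting.

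- **That an EUC participant cured locally cannot count as cured.** Section IV.F does not say that only the study sample counts, and no passage sets missing SVR12 to failure. The stated method is multiple imputation. The intent-to-treat paragraph attributes attrition to starting and completing therapy, not to missed tests.
- **That H2 is biased toward MTC.** Lower EUC attendance is an assumption. Follow-up visits, RNA testing and payments are the same in both arms, and the van's harm reduction services are open to all who began study procedures. If cured and uncured participants within an arm were equally likely to be missing, MAR imputation by arm would leave no bias.
- **That failed draws add to the bias.** No arm difference is stated, and people from whom no venous sample can be obtained are excluded at entry. The Background figure that "26% of individuals with a positive rapid HCV test did not obtain confirmatory testing, largely because of poor venous access" comes from the earlier UG3 phase, before any such exclusion.

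It can also be said that one laboratory and one time point is an arm-neutral standard, that record results would arise mainly in EUC, and that rules for a missing measurement often sit in an SAP, which is not shown here.

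These points limit the claim. They do not remove it. The protocol has itself fixed the source of a primary endpoint, and navigation does end before the visit. Imputing an outcome that can be read in a chart is a weaker choice than requesting it, and MAR fails in the case described.

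**Conclusion.** The point holds as a conditional risk. What is certain from the text is that section IV.F names a single source for SVR12 and no fallback, while the means to obtain community results are already secured from every participant. A bias in H2 toward MTC follows only if cured EUC participants miss the study sample more often than cured MTC participants, which is plausible but not stated.

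On the illustrative 80% and 90% ascertainment at 40% true cure, the spurious difference is about 3 points under MAR imputation and 4 points with missing as failure. At 70% and 90% it is about 6 and 8 points. The planned difference is 18.5 points. A reader might infer that the gap could trigger an early efficacy stop. On these scenarios that chance is only about 0.6% to 1.9%, so the interim rule is not a main reason to act. The change is worth making because it is cheap and replaces imputed values with observed ones.

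**What to change.** In section IV.F, state that when the study venous sample is missing, SVR12 may be taken from a venous HCV RNA result in the community medical record. The result should fall in a stated window that opens 12 weeks after the end of treatment and has an upper limit, so that later samples affected by reinfection are not admitted. Request records under criterion (h) for every randomised participant who lacks the study sample, by the same procedure in both arms.

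Report the source of SVR12 by arm, and give a sensitivity analysis using study samples only. After a failed draw, use the paired DBS result in a sensitivity analysis only. It should not define cure, because DBS is the test under validation in the same section and the Background warns of false negatives at low viral titres. Keep the DBS accuracy analysis to participants with both samples.

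The cost is protocol wording and record requests already covered by the releases; no visit or procedure is added. The downside is that results would come from more than one laboratory, and record results may arise more often in EUC. The source table and the study-sample-only analysis show how much depends on this.

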#### **G. Qualitative Formative Evaluation**

**Systematic Observation and Evaluative Ethnography.** MPI [name] will lead the systematic observation of the UH3 intervention in action and evaluative ethnography capturing the complexity of the overall syringe services and HCV telehealth implementation process within the larger harm reduction context, on and around the van. We will conduct a series of observation episodes and take detailed ethnographic field notes at selected sites where the UH3 prevention and treatment van provides services. Observations and ethnographic field notes will be directed by a guide that will aim to capture the following:

- 1) Description of the harm reduction and HCV care continuum setting (nature of setting, time of day, month, spatial arrangements of people in the settings);
- 2) Details on how syringe services and HCV telehealth are used, including implementation, ease of use, staff interactions, experiences and reflections;
- 3) Description of syringe service and HCV telehealth staff (services offered, skills, rapport with clients);
- 4) Description of clients utilizing syringe service and HCV telehealth, their sociodemographic characteristics (e.g., sex, race/ethnicity, age), drugs of choice, and unique needs;
- 5) The interactions between staff and clients (type of interaction, casual conversation topics, disposition of staff toward clients and vice versa, services provided).

We will record all observations that appear to be pertinent to our core programmatic evaluation. From what we learn from these observations, we will develop a list of questions to ask in the form of "on the spot interviews" with service providers and clients. We will focus on the following guiding topics: a) implementation; b) acceptability; c) feasibility; d) participant perceptions; e) staff, provider, and partner perceptions at UH3 mobile sites and local harm reduction and public health agencies; f) barriers, facilitators, successes, challenges and lessons-learned; g) larger relationships between the syringe service and HCV telehealth van and the harm reduction and HCV care continuums; and, h) sustainability. We will ask questions focused on these topics whenever possible, before or immediately after the encounter between service providers and clients. Recorded data from these ethnographic observations, conversations, and information elicited from "on the spot interviews" will be transcribed and entered into a word processing software as textual/content data for subsequent analysis.

**H. Qualitative Data Analysis.** Our team will conduct qualitative analyses in two stages: open coding, and re-coding by application of codes from the coding manual developed in the study. Through secondary coding, we will group first-generation codes into larger themes. We will enter coded text and coding tree into Dedoose v8, which will allow us to group segments from all documents by code in a secure cloud-based system that is ideal

for cross-site coding and analysis. By creating a database that can be indexed by topic or theme, we will be able to identify patterns, clusters, and relationships across all cases in the data, such as experiences with syringe services and HCV telehealth, perceived benefits and challenges with services among stakeholders, and knowledge, attitudes and beliefs about van-based syringe services and HCV treatment among PWIDs.

We will enter preliminary ideas for codes in Dedoose following initial readings of transcripts. This process will continue until the conceptual categories are exhausted or when few new ideas emerge that have not already been noted (i.e., when we achieve thematic saturation). We expect to reach saturation following approximately 75 interviews including study staff working on/around the van, harm reduction and public health stakeholders, telemedicine and community healthcare providers and study participants. Next, our DISCERNNE qualitative research team members will refine and reduce the number of open codes by comparing and contrasting them and defining the limits or boundaries of particular conceptual categories. This process will continue iteratively until acceptable inter-coder reliability has been achieved. The remaining transcripts will then be divided among the coding team members and independently coded by the five team members as we have done in the UG3 phase. The coding team will continue to meet regularly via videoconference (e.g., Zoom) to resolve coding questions. Once the coding manual is final and data are coded, we will begin the analytic process. We will use thematic analysis to identify salient patterns in the data with regard to harm reduction and HCV treatment care continuum experiences on the van. In addition to providing an improved understanding of the intervention elements that facilitate or impede implementation, the formative evaluation will be used to optimize the intervention during the remaining time in the project.

#### **IV. DATA AND SAFETY MONITORING**

The conduct of all human studies research carried out during the UH3 phase will follow guidelines established by the National Executive Steering Committee, NIDA, and local IRBs. Research subjects for the proposed project will include key informant public health stakeholders (i.e., local/regional clinicians), Persons Who Inject Drugs (PWID), study staff (i.e., staff working on/around the van; telemedicine clinicians), and the staff of harm reduction agencies in rural counties in the states of Vermont and New Hampshire.

##### ***A. Statement of responsibility.***

The mPIs are responsible for data safety and monitoring for the project, as well as developing and executing a Data & Safety Monitoring Plan (DSMP), which will be reviewed and monitored by the NIDA Program Officer, the Baystate IRB and a Data Safety and Monitoring Board (DSMB). The DSMP will be completed and approved by the Program Officer, the Baystate IRB and DSMB before data collection commences. The study will monitor adverse effects and collect information that will allow the intervention to be used safely.

##### ***B. DSMB plan.***

A DSMB will be established to monitor the safety of the subjects, the study/data validity, the effectiveness of the medications under study, and any unexpected effects. The DSMB will ensure immediate and appropriate response to any sign of harmful effects with the potential to justify stopping study activities.

*Composition.* We propose a 3-person DSMB that includes a physician expert in addictions, an epidemiologist or biostatistician, and an individual representing the interests of the affected population. They will have neither professional nor financial interests in the study outcome, and will not be employed by the funding agency. Each member will bring expertise in the varied scientific disciplines needed to interpret the data and ensure participant safety. Resumes will be made available to the Program Officer and IRB.

*Charge.* The DSMB is charged with ensuring the safety of individuals participating in this study. Its activities will include reviewing any AEs or SAEs that occur, approving and overseeing the plan for interim data analysis,

and preparing written reports to inform the mPIs, as well as the Program Officer, of the impact of the research on the safety of the participants.

*Frequency of DSMB reviews.* The DSMB will meet via videoconference at the discretion of its Chair, but at a minimum 3 times – (1) prior to the commencement of data collection to review (and revise as necessary) the detailed DSMP (which will have been approved by the Program Officer and IRB), and ensure that a clear protocol for study monitoring is operational prior to data collection activities, (2) after the first 25% of subjects completes end-of-treatment assessment, and (3) after the first 50% subjects completes 12-week follow-up.

*Content of DSMB report.* The DSMB will send a report to the NIDA Program Officer within a month after each DSMB meeting, which will include meeting dates, meeting agenda and minutes, changes in membership (including qualifications and conflicts of interest for any new members), and DSMB recommendations for the study.

